# Cognitive behavioural therapy for insomnia in patients with rheumatoid arthritis: protocol for the randomised, single-blinded, parallel-group Sleep-RA trial

**DOI:** 10.1186/s13063-020-04282-6

**Published:** 2020-05-29

**Keywords:** Inflammatory arthritis, Insomnia, Sleep disturbance, Cognitive behavioural therapy for insomnia, Non-pharmacological treatment, Polysomnography, Actigraphy, Fatigue, Impact of rheumatoid arthritis, Health-related quality of life

## Abstract

**Background:**

More than half of patients with rheumatoid arthritis complain of insomnia, which is predominantly treated with hypnotic drugs. However, cognitive behavioural therapy for insomnia is recommended as the first-line treatment in international guidelines on sleep. Patients with rheumatoid arthritis suffer from debilitating symptoms, such as fatigue and pain, which can also be linked to sleep disturbance. It remains to be determined whether cognitive behavioural therapy for insomnia can be effective in patients with rheumatoid arthritis. The aim of the Sleep-RA trial is to investigate the efficacy of cognitive behavioural therapy for insomnia on sleep and disease-related symptoms in patients with rheumatoid arthritis. The primary objective is to compare the effect of cognitive behavioural therapy for insomnia relative to usual care on changes in sleep efficiency from baseline to week 7 in patients with rheumatoid arthritis. The key secondary objectives are to compare the effect of cognitive behavioural therapy for insomnia relative to usual care on changes in sleep onset latency, wake after sleep onset, total sleep time, insomnia, sleep quality, fatigue, impact of rheumatoid arthritis and depressive symptoms from baseline to week 26 in patients with rheumatoid arthritis.

**Methods:**

The Sleep-RA trial is a randomised controlled trial with a two-group parallel design. Sixty patients with rheumatoid arthritis, insomnia and low-to-moderate disease activity will be allocated 1:1 to treatment with cognitive behavioural therapy for insomnia or usual care. Patients in the intervention group will receive nurse-led, group-based cognitive behavioural therapy for insomnia once a week for 6 weeks. Outcome assessments will be carried out at baseline, after treatment (week 7) and at follow-up (week 26).

**Discussion:**

Data on treatment of insomnia in patients with rheumatoid arthritis are sparse. The Sleep-RA trial is the first randomised controlled trial to investigate the efficacy of cognitive behavioural therapy for insomnia in patients with rheumatoid arthritis. Because symptoms of rheumatoid arthritis and insomnia have many similarities, we also find it relevant to investigate the secondary effects of cognitive behavioural therapy for insomnia on fatigue, impact of rheumatoid arthritis, depressive symptoms, pain, functional status, health-related quality of life and disease activity.

If we find cognitive behavioural therapy for insomnia to be effective in patients with rheumatoid arthritis this will add weight to the argument that evidence-based non-pharmacological treatment for insomnia in rheumatological outpatient clinics is eligible in accordance with the existing international guidelines on sleep.

**Trial registration:**

ClinicalTrials.gov: NCT03766100. Registered on 30 November 2018.

## Administrative information

The numbers in curly brackets in this protocol refer to the Standard Protocol Items: Recommendations for Interventional Trials (SPIRIT) checklist item numbers. The order of the items has been modified to group similar items (see http://www.equator-network.org/reporting-guidelines/spirit-2013-statement-defining-standard-protocol-items-for-clinical-trials/).

## Introduction

### Background and rationale {6a}

#### Rheumatoid arthritis

Rheumatoid arthritis (RA) is a chronic autoimmune inflammatory disease with a prevalence worldwide of 0.4–1.3%. Women are affected three times more frequently than men, and onset is most often at 50–60 years of age [1, 2]. Symptoms include joint swelling, pain and stiffness, and often significant disability. Disease activity is most commonly monitored with Disease Activity Score-28 C-reactive protein (DAS28-CRP) based on the number of swollen joints, the number of tender joints, serum CRP and patient global assessment [3, 4]. Improvements in early diagnosis and medical treatment with anti-rheumatic drugs have led to a reduced incidence of swollen and tender joints, pain and joint destruction [5]. Nevertheless, patients still report a wide range of symptoms with a high prevalence; among the most frequently reported are sleep disturbances, fatigue, depressive symptoms, pain, reduced functional status and health-related quality of life (HRQoL) [6–8]. In evaluating their medical treatment with antirheumatic drugs, patients indicate that sleep is one of the most important parameters. This highlights the major impact that sleep has on physical and mental well-being [9, 10].

Sleep disturbances are common in patients with RA, with a prevalence of 60–80% compared to 10–30% in the general population [11–13]. Furthermore, sleep quality can be associated with disease activity; for example, patients with moderate and high disease activity reported fewer hours asleep than patients with low disease activity or those in remission [14–17]. Sleep disturbances in patients with RA are characterised by significantly worse sleep efficiency (SE), sleep quality, sleep latency, number of awakenings, and time awake after sleep onset than healthy control groups [14, 18–20].

#### Insomnia

According to the International Classification of Sleep Disorders third edition (ICSD-3) and the Diagnostic and Statistical Manual of Mental Disorders the diagnostic criteria for insomnia are: sleep initiation or maintenance problems; inadequate opportunity and circumstances to sleep; and daytime consequences [21, 22]. The ICSD-3 duration criterion for chronic insomnia disorder is 3 months and a frequency criterion of at least three times per week [21]. Like RA, insomnia is associated with fatigue, depressive symptoms, pain, functional status and cardiovascular diseases [23–25].

The association between disease activity and sleep is acknowledged in patients with inflammatory arthritis, but the exact underlying mechanisms of insomnia in general have not been identified. Insomnia is often considered to be linked to hyperarousal, which decreases the likelihood of sleep; however, the heterogeneity in cause, symptoms, course, comorbidities and consequences complicates the establishment of a universal aetiological or pathophysiological model of insomnia [26, 27]. According to existing evidence on the pathophysiology of insomnia, insomnia is most likely to develop in people who have increased genetic risk and who experience abnormalities in neurobiological processes—vulnerabilities that may lead to hyperarousal and to psychological and behavioural processes that increase the risk for developing insomnia [27–29].

According to the conceptual “3P model” of insomnia by Spielman et al., three elements contribute to the development and maintenance of chronic insomnia: predisposing factors, precipitating events, and perpetuating mechanisms [30]. The predisposing factors include the fact that some individuals may have an increased risk of insomnia by having certain genetic predisposing factors of personal vulnerability that might contribute to a highly sensitive or malfunctioning biological sleep system or a hyperactive arousal system that interferes with sleep [31]. The time of diagnosis can be a precipitating event as being diagnosed with a chronic disease like RA can cause a cognitive and emotional reaction. These reactions can manifest as worry or depressed mood, which may also exploit the vulnerability of a highly reactive sleep system [32]. For patients already diagnosed with RA, several conditions related to their arthritis can represent precipitating events that contribute to the development of insomnia—for example, fatigue, pain, reduced functional status, flares and disease activity [33–35].

When insomnia becomes chronic, sleep is characterised by inappropriate habits and dysfunctional thoughts related to sleep, i.e. the perpetuating mechanisms. Insomnia is often linked to maladaptive strategies, such as avoidance behaviour during waking hours. Avoidance behaviour may include cancelling planned activities either because of feeling too tired or due to fear that the activities will interfere with sleep. Also, increased sleep effort is common, e.g. spending excessive time in bed and developing rigid sleep-related rituals. In response to insomnia, some people also develop sleep-interfering cognitions, such as overestimating and worrying about the negative consequences of insomnia and approaching bed time with fear of failure [30, 36].

#### Treatment of insomnia

The predominant treatment for insomnia is hypnotic drugs [37]. However, hypnotic drugs cause many side effects, including increased risk of falls resulting in fracture, cognitive impairment, impaired motor coordination, sedation, confusion, motor vehicle accidents, tolerance and dependence [38, 39], and are associated with increased mortality and risk of dementia [40–42]. In the search for non-pharmacological treatments for insomnia without severe side effects and with longer-lasting effects, clinical trials have tested the effects of exercise, thought control, imagery training, acupuncture, paradoxical intention, mindfulness and cognitive behavioural therapy for insomnia (CBT-i) [43–45]. Currently, non-pharmacological treatment for insomnia in patients with RA has focused only on physical activity and exercise training [46, 47].

However, hypnotic drugs do not address the precipitating events or perpetuating mechanisms that maintain chronic insomnia, and precipitating events or perpetuating mechanisms are not the primary focus or purpose of physical activity or exercise training. Furthermore, some patients can be disabled to a degree that inhibits them engaging in physical activity or exercise training. CBT-i is recommended as the first-line treatment for insomnia as it has demonstrated more effects than hypnotic drugs and has demonstrated a long-term effect [48–51]. In clinical settings, CBT-i is most often carried out by psychologists; however, treatment with CBT-i in groups led by nurses has been tested and the results showed significant positive effects [52, 53].

According to Morin and his model “The vicious circle of persistent insomnia”, the effect of CBT-i is caused by its ability to modify thought patterns and behaviours that reinforce poor sleep [54]. Thus, it is highly relevant to investigate the efficacy of CBT-i in patients with RA and, to our knowledge, this is the first clinical trial to investigate CBT-i in this population.

### Objectives {7}

Our primary objective is to compare the effect of CBT-i relative to usual care on changes in SE from baseline to week 7 in patients with RA.

Our key secondary objectives are to compare the effect of CBT-i relative to usual care on changes in sleep onset latency (SOL), wake after sleep onset (WASO), total sleep time (TST), insomnia, sleep quality, fatigue, impact of RA and depressive symptoms from baseline to week 26 in patients with RA.

Other secondary objectives are to compare the effect of CBT-i relative to usual care on changes in SE, SOL, WASO, TST, insomnia, sleep quality, fatigue, impact of RA, depressive symptoms, disease activity, tender joints, swollen joints, acute-phase reactant value, patient global assessment, physician global assessment, pain, functional status and HRQoL from baseline to weeks 7 and 26 in patients with RA.

### Trial design {8}

The Sleep-RA trial will be carried out as a randomised controlled trial with a two-group parallel design. Participants (*n* = 60) will be allocated 1:1 to either CBT-i as treatment (intervention group) or to usual care (control group). Outcome assessments will be conducted three times for each participant: at baseline, after treatment (week 7) and at follow-up (week 26), as presented in Fig. 1.

**Fig. 1 Fig1:**
[figure not shown]
Study flowchart

## Methods: participants, interventions and outcomes

### Study setting {9}

We will recruit patients from hospital rheumatology outpatient clinics in The Capital Region of Denmark and Region Zealand are the official names of the two regions we recruite participants from.

### Eligibility criteria {10}

#### Inclusion criteria

Participants will be included if they: are diagnosed with RA according to the American College of Rheumatology/European League Against Rheumatism 2010 criteria [55]; have low to moderate disease activity, defined as DAS28-CRP ≤5.1 [4] and are 18 years of age or older; have both insomnia, defined as Insomnia Severity Index ≥11 [56] and chronic insomnia, according to the ICSD-3 duration criterion [29, 57]; have unchanged treatment with anti-rheumatic drugs for the preceding 3 months and no indication for changes of treatment with antirheumatic drugs during the intervention; and are able to understand and read Danish.

#### Exclusion criteria

Patients will be excluded if they: have had glucocorticoid administered by intramuscular, intra-articular or intravenous methods within the preceding 4 weeks; are on a continuous current daily intake of oral glucocorticoids >5 mg/day; have had a change in oral glucocorticoid dose within the preceding 3 months; have had prior or current professional non-pharmacological treatment for insomnia; work at night during the intervention, are pregnant or nursing a baby; have a current alcohol or drug-use disorder, according to their medical journal; have patient-related circumstances (physical or mental) that impede their ability to give informed consent and adhere to the programme.

### Who will take informed consent? {26a}

The corresponding author ([name]) is the project manager of Sleep-RA and will obtain informed consent from participants.

### Additional consent provisions for collection and use of participant data and biological specimens {26b}

On the consent form, participants are asked to sign if they agree to have been given written and oral information on the purpose, method, advantages and disadvantages of saying yes to participate in the trial, and if they agree to participate voluntary. On the consent form, participants are informed that they can withdraw the consent without losing any rights to treatment, either current or future. They are also asked if they agree to the use of their data should they choose to withdraw from the trial.

This trial does not involve collecting biological specimens for storage.

### Interventions

Both groups will continually receive relevant treatment for their RA.

### Explanation for the choice of comparators {6b}

There are no standards on when and how to identify sleep disturbances in rheumatology outpatient consultations. Participants in the control group will receive usual care on sleep, which in the rheumatology outpatient clinics in The Capital Region of Denmark and in Region Zealand is sporadic and random and conducted via casual conversations based on the general knowledge of rheumatologists or nurses. Participants in the control group will be encouraged by [name] to maintain their usual everyday lives and sleep patterns until follow-up assessment is conducted.

### Intervention description {11a}

In the Sleep-RA trial, CBT-i is a 6-week intervention with participant attendance of 2 h per week. The intervention will be conducted in groups of two to six participants per group. All sessions will be conducted by [name], who is a trained nurse in CBT-i.

The manual for the CBT-i intervention in Sleep-RA has been developed by [name], [name] and [name] in collaboration with a clinical psychologist trained in CBT-i and patient research partners, in accordance with the “Template for Intervention Description and Replication” checklist and guide [58]. The manual is guided by theory on CBT-i, available evidence and previous CBT-i manuals [54, 59–66]. The CBT-i intervention consists of sleep education, stimulus control, sleep restriction, cognitive therapy and relaxation, as presented in Table 1. The CBT-i intervention includes presentations by [name], exchanges of experiences, assignments, relaxation exercises and individual and shared discussions and reflections on how to use the knowledge gained during the intervention and changed habits related to sleep in daily life.

**Table 1 Tab1:** Cognitive behavioural therapy for insomnia: intervention overview

**Session 1**	Introduction	Presentation
		Goals
		Expectations
	Sleep education	Normal sleep and its determinants
		Sleep needs
		Consequences of insomnia
		Nature of insomnia
		Evaluation of participant sleep
		Sleep hygiene
	Sleep restriction	Introduce sleep diary
**Session 2**	Follow-up	Since last session
	Sleep education	Sleep hygiene
	Stimuli control	Rationale; conditioned arousal
		Instructions
	Sleep restriction	Rationale; sleep drive and sleep consolidation
		Sleep efficiency and sleep window for week 2
	Relaxation	Bed time wind-down
**Session 3**	Follow-up	Since last session
	Stimuli control	Experiences and challenges
	Sleep restriction	Experiences and challenges
		Sleep efficiency and sleep window for week 3
	Cognitive therapy	Cognitions affecting sleep
		Cognitive techniques to treat insomnia
**Session 4**	Follow-up	Since last session
	Sleep restriction	Experiences and challenges
		Sleep efficiency and sleep window for week 4
	Cognitive therapy	Experiences and challenges
		Cognitive techniques to treat insomnia
		Worry-time
	Relaxation	Rationale, break the tension and return to a relaxed state
		Body scan meditation
**Session 5**	Follow-up	Since last session
	Stimuli control	Experiences and challenges
	Sleep restriction	Experiences and challenges
		Sleep efficiency and sleep window for week 5
	Cognitive therapy	Experiences and challenges
		Cognitive techniques to treat insomnia
	Relaxation	Experiences and challenges
**Session 6**	Follow-up	Since last session
	Sleep restriction	Experiences and challenges
		Sleep efficiency and sleep window for week 6
	Closure	Plan for further work
		Relapse prevention

### Criteria for discontinuing or modifying allocated interventions {11b}

If a participant in the intervention group is not able to participate in one CBT-i session due to unforeseen circumstances, an individual session is planned as soon as possible.

### Strategies to improve adherence to interventions {11c}

Adherence enhancement strategies are in use throughout the trial period, e.g. patients are informed of the importance of adhering regardless of allocation, and participants are offered reimbursements for travel [67].

#### Relevant concomitant care permitted or prohibited during the trial {11d}

Participants are prohibited from participating in any professional non-pharmacological treatment for insomnia other than Sleep-RA during the trial period.

### Provisions for post-trial care {30}

Participants allocated to the control group will be offered a nurse consultation in the rheumatology outpatient clinic with a focus on sleep when follow-up assessment is conducted.

### Outcomes {12}

#### Primary outcome

The primary outcome is SE at week 7 assessed by polysomnography (PSG) [68]. SE percentage = (TST/total time in bed (lights out to lights on)) × 100. In healthy persons, SE is 85–90%.

PSG is a comprehensive study of the biophysiological changes that occur in the human body during sleep. In Sleep-RA, 17 electrodes will be attached to each participant, recording data from electroencephalogram, eye movements electro-oculogram, electromyogram muscle activity or skeletal muscle activation, heart rhythm, respiratory airflow, respiratory effort and peripheral pulse oximetry [69]. All PSG studies will be conducted in the participants’ own homes. Data from PSG will be analysed in epochs of 30 s and managed at the Danish Center for Sleep Medicine (DCSM), Rigshospitalet, Glostrup.

#### Key secondary outcomes

We will examine the effect of improved sleep on key sleep outcomes and key RA outcomes at follow-up at week 26 if CBT-i has a significant positive effect on the primary outcome of SE after treatment at week 7, as presented in Fig. 2.

**Fig. 2 Fig2:**
[figure not shown]
Statistical method for key secondary outcomes

##### Key sleep outcomes

SOL will be assessed with PSG. SOL is the amount of time it takes to go from being fully awake to being asleep [70].

WASO will be assessed with PSG. WASO is the cumulative time awake between sleep onset and the final morning awakening [70].

TST will be assessed with PSG. TST is the cumulative time asleep between sleep onset and the final morning awakening [70].

Insomnia will be assessed with the Insomnia Severity Index questionnaire. This is a seven-item questionnaire designed to evaluate insomnia severity based on difficulties falling asleep, night-time awakenings, early morning awakenings, impairment of daytime functioning due to sleep problems, noticeability of impairments, distress or worry caused by sleep difficulties and dissatisfaction with sleep over the past 2 weeks. Each item is rated using a five-point Likert scale ranging from 0 (not at all) to 4 (very much), for a total score ranging from 0 (no insomnia) to 28 (clinical insomnia) [71]. A cut-off of 11 has been validated in a clinical sample of people with insomnia and demonstrated a sensitivity of 97.2% and a specificity of 100% [56].

Sleep quality will be assessed with the Pittsburgh Sleep Quality Index (PSQI) questionnaire. The PSQI measures self-reported sleep over the past 4 weeks [72]. It includes nine items/18 questions with seven categories, including subjective sleep quality, sleep latency, sleep duration, habitual SE, sleep disturbances, use of sleep medications and daytime dysfunction. A global sum score for the PSQI >5 indicates poor sleep. The Cronbach’s α value for the PSQI is 0.83 [73].

##### Key RA outcomes

Fatigue will be assessed with the Bristol Rheumatoid Arthritis Fatigue Multidimensional Questionnaire (BRAF-MDQ) for the previous 7 days [74]. The BRAF-MDQ consists of 20 items with the opportunity to define five domains: total fatigue, physical fatigue, living with fatigue, cognitive fatigue and emotional fatigue. The total score ranges from 0 to 70, with a higher score indicating more severity. The Cronbach’s α value for BRAF-MDQ is >0.93 [75].

The impact of RA on daily life will be assessed with the Rheumatoid Arthritis Impact of Disease (RAID) questionnaire [76, 77]. RAID consists of seven items, each of which is rated using a numerical rating scale of 0–10 with higher scores indicating more severity, covering pain, physical function, fatigue, sleep, physical well-being, mental well-being and coping for the previous 7 days. The Cronbach’s α value for RAID is >0.93 [75].

Depressive symptoms will be assessed with the Hospital Anxiety and Depression Scale-Depression (HADS-D) [78]. HADS-D measures depressive symptoms in the previous 7 days. Seven items are rated on a four-point scale and scored from 0 to 3, with total scores ranging from 0 to 21. Scores between 0 and 7 represent ‘no case’, 8 to 10 indicate ‘possible case’, 11–15 ‘moderate case’ and ‘15–21’ suggest a ‘probable severe case of depression’ [79]. The Cronbach’s α value for HADS-D is 0.82 [80].

#### Other secondary outcomes

We will examine other secondary outcomes after treatment at week 7 and at follow-up at week 26 if CBT-i has a significant positive effect on the primary outcome of SE after treatment at week 7.

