### Statistical methods

#### Statistical methods for primary and secondary outcomes {20a}

All main analyses will be conducted based on the intention-to-treat (ITT) population. We plan to conduct both an analysis of the full analysis set (patients with outcome data available at baseline) and a per-protocol analysis so that any differences between them can be explicitly discussed and interpreted. The ITT principle states the effect of a treatment policy (i.e. the planned treatment regimen) rather than the actual treatment given. The consequence of conducting ITT analyses is that participants allocated to a treatment group should be followed up, assessed and analysed as members of that group, irrespective of their compliance to the planned course of treatment. Robustness is a concept that refers to the sensitivity of the overall conclusions to various limitations of the data, assumptions and analytic approaches to data analysis. Robustness implies that the treatment effect and primary conclusions of the trial are not substantially affected when analyses are carried out based on alternative assumptions or analytical approaches.

We will control the α level across only the most important hypotheses by use of a hierarchical testing strategy to preserve a type 1 error rate of 5% for the primary outcome of change in SE assessed after treatment at week 7, followed by SE assessed at follow-up after 26 weeks. All the patient-reported outcome measures and other secondary outcome measures will, by principle, only be clinically relevant after 26 weeks. The sleep-related key secondary outcomes (SOL, WASO, TST, insomnia and sleep quality) will only be considered statistically significant with a *P* value <0.01 (0.05/5). The RA-related key secondary outcomes (fatigue, impact of RA and depressive symptoms) will only be considered statistically significant with a *P* value <0.017 (0.05/3) as described in Fig. 2.

In the Sleep-RA trial with repeated measures, participants will be randomly assigned to treatment groups, and outcome observations are made at two time points on each patient. We anticipate that measures on the same patient at different times are correlated and that measures taken close together in time will be more highly correlated than measures taken further apart in time; observations on different patients will be assumed to be independent.

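### The plan makes examination of every secondary outcome, not just significance claims, conditional on a positive week-7 result, in conflict with its own unconditional objectives

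*Protocol article*

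**What the plan says.** Four parts of the protocol article bear on this.

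- **Key secondary outcomes.** The effect on the key sleep and RA outcomes will be examined "at follow-up at week 26 if CBT-i has a significant positive effect on the primary outcome of SE after treatment at week 7". The sentence points to Fig. 2, whose caption describes a statistical method; the figure itself is not visible in the text at hand.
- **Other secondary outcomes.** The same condition, again referring to week-7 sleep efficiency, is repeated: "We will examine other secondary outcomes after treatment at week 7 and at follow-up at week 26 if CBT-i has a significant positive effect". Together the two sections cover the whole secondary set.
- **Objectives {7}.** The comparisons are listed with no condition: "Other secondary objectives are to compare the effect of CBT-i relative to usual care on changes in SE, SOL, WASO, TST, insomnia, sleep quality", and so on through disease activity, joint counts, pain, function and quality of life, at weeks 7 and 26. The Sample size section likewise refers, without a condition, to exploratory analyses of any secondary outcome collected at week 26.
- **Statistical methods {20a}.** "We will control the α level across only the most important hypotheses by use of a hierarchical testing strategy". The sequence given is sleep efficiency at week 7, then sleep efficiency at week 26. Thresholds are set only for the eight key secondary outcomes: 0.01 for each of five sleep outcomes and 0.017 for each of three RA outcomes. The other secondary outcomes receive no alpha. The same section describes one repeated-measures model that holds the between-group comparisons at both visits.

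**The concern.** A hierarchical procedure normally decides what may be claimed as statistically significant. Here the condition is attached to whether the outcomes are examined at all. For the key secondaries, the pointer to a statistical-method figure makes it easy to read the sentence as a testing rule. That reading is harder to sustain for the other secondaries, which lie outside the formal alpha allocation and are presumably descriptive or exploratory.

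If the sentences were followed literally after a non-significant primary, there would be no between-group estimates for insomnia severity, fatigue, depressive symptoms, pain, function, quality of life, DAS28-CRP, joint counts or CRP. The condition requires a significant positive effect, so it also fails when CBT-i does worse than usual care. The availability of results would then depend on the primary result, which biases later evidence synthesis. The article describes this as the first randomised trial of CBT-i in RA, so little other evidence would fill the gap.

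**Working it through.** **1. The sections side by side**

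| Section | Secondary outcomes covered | Condition |
|---|---|---|
| Key secondary outcomes | eight key outcomes, week 26 | significant positive week-7 sleep efficiency |
| Other secondary outcomes | all others, weeks 7 and 26 | same |
| Objectives {7} | key and other (18 listed under other secondary) | none |
| Sample size {14} | any secondary, week 26 | none |
| Statistical methods {20a} | eight key outcomes | significance thresholds, after a sequence that includes week-26 sleep efficiency |

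If the primary is not significant, the first two rows and the next two cannot all be followed. The first and last rows also differ on the gate itself: week-7 sleep efficiency alone, or week 7 followed by week 26.

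**2. What survives a closed gate.** The primary model includes time and the group-by-time interaction, so polysomnographic sleep efficiency at week 26 is estimated in any case. Nothing comparable is stated for the other outcomes.

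**3. Reproducing the plan's power.** Inputs from Sample size {14}: difference 6 points, SD 7.5, two-sided alpha 0.05, 30 per group, or 26 per group after four withdrawals in each. For a pooled t test, df = 2n − 2 and the noncentrality is δ / (SD × √(2/n)).

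- n = 30: 6 / (7.5 × √(2/30)) = 6 / 1.936 = 3.098; df = 58; critical value 2.002; power 86.1%. The plan states 86.1%.
- n = 26: 6 / (7.5 × √(2/26)) = 6 / 2.080 = 2.884; df = 50; critical value 2.009; power 80.7%. The plan states 80.7%.

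**4. Probability that the gate closes.** This is P(T < critical value), with T noncentral t, because the gate needs a significant result in favour of CBT-i. Only the 6-point row uses the plan's own effect; the others are assumed values, shown as a range.

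| True difference | 30 per group | 26 per group |
|---|---|---|
| 6 (plan) | 13.9% | 19.3% |
| 5 (assumed) | 28.1% | 34.6% |
| 4.5 (assumed) | 37% | 44% |
| 4 (assumed) | 47.2% | 52.9% |
| 3 (assumed) | 66.9% | 70.7% |
| 0 (no effect) | 97.5% | 97.5% |

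**5. What the gate does protect.** If CBT-i affects nothing, a false positive secondary claim is possible only when the gate opens, so its probability is at most 0.05 / 2 = 2.5%. That is weak familywise control. It covers only the case of no effect on anything, and once the gate opens it does not limit errors among the other secondary outcomes. It is still a real reason to gate claims. Estimates with confidence intervals, reported without a significance claim, do not use up that protection.

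**The case against.** The best defence is that the condition is a testing gate, loosely worded. The key-secondary sentence refers to a statistical-method figure, and the statistical section works through what may be considered significant, which is a rule about claims. The sentence for the other secondaries repeats the same condition in nearly the same words. The Objectives, the sample size section and the missing-data section (which plans to analyse all variables with missing data) carry no condition. All data are collected regardless. A statistical analysis plan, if one exists, could settle what is reported after a negative primary.

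Much of this stands. A reader might infer that the investigators intend to withhold secondary results; no section says so, and the unconditional sections point the other way. A reader might also infer that, with no alpha assigned to the other secondaries, the gate protects no error rate; step 5 shows that it gives weak familywise protection. Nor should the disease-activity measures be presented as the trial's safety data: they are listed as outcomes, and monitoring of unintended events is separate and ungated.

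What the defence does not remove is the contradiction. The two gating sentences use a verb that covers analysis as a whole, and no section says that secondary estimates will be produced when the gate is closed.

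**Conclusion.** The point holds as a fault of wording and consistency. Taken literally, the two gating sentences make the availability of almost all secondary results depend on the primary result, and they conflict with the Objectives and sample size sections. Gating significance claims is sound; gating estimation and reporting is not.

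The gate closes with probability 13.9% to 19.3% if the planning effect is exactly true, and more often for smaller effects. These figures are one minus power for an unadjusted t test. The planned model adjusts for baseline, so the actual probabilities may be lower; the article gives no baseline to week-7 correlation from which to compute them. They should not be read as the chance that results will be suppressed, because that would also require the literal reading to be the one applied.

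The primary comparison, sample size, primary alpha, power and the 0.01 and 0.017 thresholds are unaffected.

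**What to change.** In the sections on key and other secondary outcomes, replace the condition with: *All secondary outcomes will be estimated and reported with 95% confidence intervals at weeks 7 and 26 regardless of the primary result; only confirmatory significance claims for the key secondary outcomes are conditional on the hierarchy, and other secondary outcomes are exploratory.*

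Also name the gate. The key secondary section uses week-7 sleep efficiency alone, while the statistical section places week-26 sleep efficiency next in the sequence. State which of the two must be passed before the key secondary claims, and make both sections agree.

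Both changes should be made before the treatment comparison is seen, since a later choice about which secondaries to show would be open to the charge of being result-driven. The cost is two sentences plus the reconciliation, and a few extra tables if the primary is negative. The data are collected in any case.
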